## Methods/Design

The study is designed as an observational analytical population study. The population is dynamic (open for both entry and departure) and consists of all male construction workers in Denmark aged 20-59 years during the study period January 1, 1999 to December 31, 2006. The start of the study period coincides with the launching of the registration of all local workplace units in the Central Business Register in Denmark - a national register which contains primary data on all public and private businesses. The end of the study period refers to the year of the latest statistical returns on workplace size linked to local workplace unit from Statistics Denmark.

The subjects are followed one year at a time for first hospital treated injury during the year. The injuries are diagnosed on the basis of ICD-10 classification numbers S00-T98: "Injury, poisoning and certain other consequences of external causes" [23]. Included in the study are principal diagnoses as concluded either by discharge from the hospital, or by transfer to another hospital division.

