### Statistical analyses

A person will become a case once receiving a principal diagnosis in the ICD-10 interval S00-T98 ("injury, poisoning and certain other consequences of external causes") according to the OHR. For any given calendar year, a person will be censored at the time he becomes a case, emigrates or dies. Time-dependent dummy variables are used to categorise the manual workers into micro enterprises (fewer than 5 employees), small enterprises (5-9 employees), medium-sized enterprises (10-19 employees), and large enterprises (20 or more employees). A person's work category during a certain calendar year is determined by his enterprise association according to the population census performed in the end of November the preceding year.

The null hypothesis stating that "the injury rates among workers are independent of enterprise size" will be tested. If this first null hypothesis is rejected meaning that the observed injury rates most likely depend on enterprise size, a second null hypothesis will be tested. This second null hypothesis will test if "the relative rate of injury among workers in enterprises with 5-9 employees compared with other workers is independent of time period (January 1, 1999 - June 30, 2002 versus July 1, 2002 - December 31, 2005)". By this, it shall be tested if it can be assumed that the legislative change that took place in Denmark on 1 July, 2002, which cancelled the requirement of having a safety organisation in enterprises with 5 - 9 employees, did not have any effect on the injury rates among the workers in enterprises with 5-9 employees.

To deal with intra-enterprise correlations, a multi-level Poisson regression will be used to model the outcome, where the enterprises will be treated as the subjects while observations within the enterprises will be treated as correlated repeated measurements.

The analyses will be controlled for age (five-year age groups), calendar year (as categorical variable) and occupation. Occupation unit groups are: Bricklayers and stonemasons (DISCO-88 = 7122); Carpenters and joiners (DISCO-88 = 7124); Plumbers and pipe fitters (DISCO-88 = 7136); Electricians (DISCO-88 = 7137); Painters and wall-paper workers (DISCO-88 = 7141); Unskilled manual workers in construction workers (DISCO-88 = 9313).

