The analyses will be performed by use of the GENMOD procedure in SAS version 9.1. Only main effects will be considered. The empiric standard error estimates will be used and an exchangeable correlation structure is assumed. The significance level will be set to 0.05. Table 1 shows the rate ratios and 95% confidence intervals that will be calculated.

**Table 1 T1:** Manual construction workers' relative risk rates of injury, by enterprise size and type of profession

	Injury Rate Ratio	Confidence Interval (95% CI)

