The Occupational Hospitalisation Register is free of reporting bias. All hospital contacts are registered, and there are virtually no missing principal diagnoses. This can be contrasted with two alternative national data sources held by the Danish Working Environment Authority and the National Board of Industrial Injuries, respectively, to whom merely 45% of all work-related injuries are reported [30]. Another advantage of the study is that we have identification numbers on the people as well as the enterprises, which enables us to take intra-enterprise correlations into account. Since the local workplace unit number is based on each geographically bounded production unit, this study provides more precise information about workplace size than the mother company number which merely sums up the number of employed for all subordinated workplaces. The study is further strengthened by its sample size, which will afford sufficient statistical power to the various hypothesis tests.

A disadvantage of the Occupational Hospitalisation Register is that it leaves out injuries that do not need hospital treatment. Another disadvantage is that we have annual but not daily information about occupation and enterprise. Enterprise association at the time of the injury might be different from the enterprise association in the end of November the preceding calendar year and the occupational category might change during the course of the year. We believe that most of the occupational categories are quite stable since we are dealing with skilled workers. It would, for example, be unlikely that a trained carpenter would shift into a brick layer trainee in the course of a calendar year. The construction industry is, however, known for its high turnover rate [31]. Within a calendar year, a worker in a small enterprise might, for example, move to a large enterprise, where he is injured. According to our model, such an injury would erroneously be classified as having happened in a small enterprise. The size of an enterprise may also change during a calendar year. All such changes would bias our estimates toward unity; from this perspective, the estimates should be regarded as conservative. As such, we hope that our study will contribute to a better assessment of relative injury rates in small and medium-sized enterprises.

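### Clustering on enterprise alone leaves out the correlation between a mobile worker's yearly records, and exchangeable weights may move the ratios against large enterprises away from the worker-level ratio

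*Protocol article*

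**What the plan says.** The model is set out in the protocol article under Statistical analyses. Its stated purpose is limited to correlation inside enterprises: "To deal with intra-enterprise correlations, a multi-level Poisson regression will be used to model the outcome", and "the enterprises will be treated as the subjects while observations within the enterprises will be treated as correlated repeated measurements". The software is fixed ("The analyses will be performed by use of the GENMOD procedure in SAS version 9.1"), and so are the variance and the working correlation: "The empiric standard error estimates will be used and an exchangeable correlation structure is assumed".

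Follow-up is described under Methods/Design: "The subjects are followed one year at a time for first hospital treated injury during the year", "during the study period January 1, 1999 to December 31, 2006". That is eight calendar years, so one man can supply up to eight records and be a case in each. His size class for a year is "determined by his enterprise association according to the population census performed in the end of November the preceding year", so a change of employer moves his later records to another enterprise. The Discussion adds: "The construction industry is, however, known for its high turnover rate". It also says that identification numbers are held for people as well as for enterprises, but it uses this only to account for correlation within enterprises.

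**The concern.** Two features of the fixed model need attention, and they act differently.

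**Variance.** The empirical variance allows any correlation between records of the same enterprise and none between records of different enterprises. Men differ in their underlying injury risk, so one man's records are positively correlated. If he stays with one employer, they share a cluster and are covered. If he moves, the correlation across employers is left out. At stake are the intervals and P values in Table 1, for enterprise size and for occupation. The Background gives special attention to bricklayers, carpenters and plumbers, for a later project.

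**Weighting.** With a positive exchangeable correlation, a record counts for less the more records its enterprise has. Here cluster size is closely tied to the exposure, and the reference class (20 or more employees) has no upper limit. The null hypothesis concerns rates among workers. If rates differ by size within the reference class, the fitted large-enterprise rate is not the average over workers.

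**Working it through.** The article gives no event count, intra-enterprise correlation, mobility figure or interval width, so there is no stated figure to reproduce. From the document come the eight years, the 0.05 level, and two Eurostat rates in the Background used as anchors: 6,500 per 100,000 (0.065 a year) and 4,700/6,500 = 0.72. All other inputs are assumptions, shown as ranges.

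**1. Variance, closed form.** Let μ be the yearly injury rate, τ² the variance of worker risk, ω² the enterprise variance, n the workers per unit, and s the number of employers in eight years, all within one comparison group. Then

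- ρp = μτ²/[1+μ(τ²+ω²)] and ρe = μω²/[1+μ(τ²+ω²)]
- reported SE / true SE = √{[1+(8/s−1)ρp+(8n−1)ρe] / [1+7ρp+(8n−1)ρe]}

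Take μ = 0.12, τ² = 0.5, s = 4:

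- ω² = 0: ρp = 0.06/1.06 = 0.0566; ratio = √(1.0566/1.3962) = 0.87.
- ω² = 0.04, n = 30: ρp = 0.0564, ρe = 0.0045; ratio = √(2.134/2.472) = 0.93.
- ω² = 0.10, n = 30: ratio = √(3.731/4.067) = 0.96.
- ω² = 0.04-0.10: 0.88-0.89 for n = 3, and about 0.99 for n = 300.

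The loss is therefore concentrated where units are small, and the formula applies only if men stay in one comparison group.

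**2. Variance, simulation of the size contrasts.** About 11,200 workers over 8 years, 600 replicates per scenario, exchangeable-type weights, rate 0.065 or 0.15. Mean SE was divided by the empirical SD of the log rate ratios against large:

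| Assumed mobility and worker heterogeneity | SE/SD | Coverage of 95% CI |
|---|---|---|
| No moves, or no heterogeneity | 0.95-1.06 | 0.93-0.97 |
| 30% a year to any size class, τ² 0.5-1.0 | 0.95-1.04 | 0.93-0.96 |
| 30% a year within the same class, τ² 0.5-1.0 | 0.90-0.97 | 0.92-0.94 |
| 60% a year within the same class, τ² 0.5-1.0 | 0.83-0.97 | 0.90-0.95 |

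Simulation error is about 3% on SE/SD and one point on coverage. Moves across classes cost little because the shared workers make the class estimates positively correlated, and this offsets in the contrast.

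**3. Variance, occupation contrasts.** The Discussion regards occupation as stable, so a man who changes employer usually keeps his occupation and the offset is missing. A separate simulation used about 9,000 workers, 8 years, 400 replicates, fixed occupation, moves to any enterprise at 30% or 60% a year, rate 0.065 or 0.15 and τ² 0.5-1.0. It gave SE/SD 0.86-0.98 and coverage 0.90-0.94 (error about 3.5%). Without worker heterogeneity SE/SD was 0.94-1.04. The size contrasts in these runs were 0.93-1.03.

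**4. Weighting.** Weight per record is about 1/[1+(N−1)ρ], where N is the enterprise's number of records. At ρ = 0.01 over eight years:

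- 30-person unit: N = 240, weight 1/3.39 = 0.295
- 300-person unit: N = 2,400, weight 1/24.99 = 0.040, about one seventh

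At ρ = 0.001 the weights are 0.81 and 0.29.

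Effect on a ratio: suppose half of large-class workers are in 30-person units at relative rate 1.0, half in 300-person units at 0.8, and micro enterprises are at 1.2. The worker-level ratio is 1.2/0.9 = 1.33. With four years of records and ρ = 0.013 the weights are 1/2.547 = 0.393 and 1/16.587 = 0.060. The large rate becomes (0.393×1.0+0.060×0.8)/0.453 = 0.973 and the ratio 1.2/0.973 = 1.23. A GEE simulation of this layout (40 data sets) gave 1.24 with exchangeable and 1.35 with independence.

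A wider grid used units of 30, 75, 150 and 400, two distributions of workers over them, ρ 0.001-0.05, and one or eight years of records. With a constant rate inside the class, the large-class rate was unchanged at every ρ. With a gradient down to 0.72, it was 1.01-1.11 times the worker-weighted rate, so ratios against large were multiplied by 0.99-0.90.

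**The case against.** A reader might infer that the intervals are certainly too narrow. The documents do not support this. Men who stay with one employer are covered, turnover is not quantified, the population is open to entry and departure, and the Discussion's own example of turnover is a move from a small to a large enterprise, the case with almost no net effect on the size contrasts. This objection stands for certainty and for size. It does not remove the gap for moves within a class or for occupation.

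A reader might also infer that down-weighting large units narrows the intervals. It does not: the empirical variance is valid under either working correlation. In a simulation with enterprise variance only and no worker effect, the SD was 0.065 with independence weights and 0.052 with exchangeable weights. That gap reflects weighting, not under-coverage.

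A third inference is that the large reference rate is distorted. This needs a gradient inside the 20+ class, which the article does not assert. It tests a null of no relation, and its Background cites Eurostat and Danish data without a clear trend. Local workplace units also limit cluster size. Under the null the weighting causes no bias. Still, a relation with size is what the study investigates, so a gradient should not be assumed absent.

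Finally, it may be tempting to say that time-dependent size dummies make the exchangeable estimates inconsistent. No mechanism in the documents shows this, and it is not claimed here. The exchangeable structure is a defensible efficiency choice, and replacing it outright would be a trade-off between efficiency and estimand.

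**Conclusion.** The point holds in a conditional form. The stated variance ignores correlation between a mover's records in different enterprises, although person identifiers are held. Under the assumed mobility and worker heterogeneity, the reported SE for size contrasts with same-class moves is roughly 0.83-0.97 of the true value. A valid SE would then be about 3-20% larger (1/0.97 = 1.03, 1/0.83 = 1.20), with coverage of 0.90-0.95. Occupation ratios show a similar shortfall (0.86-0.98) even when men move to any enterprise, and are plausibly the more exposed. Without moves, without heterogeneity, or for size contrasts with cross-class moves, the ratio is about 1.

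Separately, if rates vary with size inside the 20+ class, exchangeable weighting shifts the ratios against large by about 1-10% under the assumed gradients, and towards one if the gradient runs in a single direction. This is a change in what is estimated, not a failure of the standard errors. The test of the 2002 legislative change was not examined.

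**What to change.** Add an analysis with an independence working correlation and a two-way robust variance:

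V = V(enterprise) + V(person) − V(enterprise × person)

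It comes from three GENMOD runs that differ only in the subject variable. The three matrices can be combined only if all runs have the same point estimates, which the independence structure ensures and the exchangeable one does not. Report the rate ratios, intervals and joint P values for size and occupation from this analysis beside the planned exchangeable fit. State that inference rests on the two-way variance if it is materially larger, and define materially larger before the results are seen. A difference in point estimates between the two fits would show whether the weighting matters.

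The cost is a little extra programming to combine the covariance matrices and rebuild the intervals and joint tests in Table 1, and somewhat wider intervals. No new data are needed, since both identifiers are already held.

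Suggested wording: *As an additional analysis, the model will be fitted with an independence working correlation and a robust variance clustered on both enterprise and person. If this variance is materially larger than the planned one, inference will be based on it.*

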Kines & Mikkelsen (2003) attempted to investigate rates of elevation fall injuries as a function of enterprise size in the Danish construction industry in the years 1993-1999 [18]. They used the following enterprise categorization: 0; 1-4; 5-9; 10-19; 20-49; 50-99; and > = 100 employees, yet their results were inconclusive; no noticeable trend was found. But as was noted by the authors, the investigation was possibly biased due to an underreporting of approximately 50% of the injuries. Moreover, enterprise size was not given in 13% of the reported injuries. Another problem with the study was that there was no control for the occupational distribution within the enterprises. According to Danish national data, injury rates among blue collar workers are on average twice as high as they are among white collar workers [19]. Also, it has been shown that injury rates differ between occupational categories among blue collar construction workers [20].

In contrast, three studies do indicate a trend of decreasing injury rates with enterprise size in the construction industry valid for the following settings: Ontario, Canada in the years 1988 to 1993 [21], South Korea in the years 1991 to 1994 [22], and Italy in the years 1995 to 2000 [8]. None of these three studies controlled for occupational distribution within the enterprises; hence, at least part of the decline in injury rates might be due to an increasing proportion of white-collar employees in the larger enterprises.

The primary aim of the present study is to investigate the relation between enterprise size and injury rates in the Danish construction industry, on a data set that is free from reporting bias, while controlling for the occupational distribution within the enterprises. A conditional aim will be to examine if there is an association between a change in Danish legislation and injury rates among construction workers in enterprises with 5-9 employees. The change, which was implemented from July 1, 2002, cancelled the requirement to have a safety organisation for enterprises with 5 - 9 employees and may have resulted in a higher risk of injury in these enterprises.

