The occupations in the employment classification module were coded according to DISCO-88 [28], which is a national version of the international standard classification of occupations (ISCO-88) [29]. DISCO-88 divides the occupations hierarchically into 10 major groups; 27 sub-major groups; 111 minor groups, and 372 unit groups. Included in the present study are the major groups related to manual construction work: group 7 "Craft and related trades workers"; group 8 "Plant and machinery operators and assemblers", and group 9 "Elementary occupations".

OHR-data of each injured individual will be linked to the latest national statistical returns of workplace size and local workplace unit. The statistical returns are assessed by Statistics Denmark every year in week 48, i.e. the last week in November, and imply that the employment data about each injured individual in the population stem from the year before the hospital treatment of the injury. Data about workplace size identifies the number of employees in addition to the owner of the workplace. Data about workplace unit identifies the local workplace unit where the injured individual was mainly carrying out his job. The local workplace unit can be the exact same as the mother enterprise unit, or it can be a unit belonging to the mother enterprise, but with a different geographical location and therefore with a different unit number. If a person worked in more than one place, which is often the case for construction workers, the local workplace unit is taken to be the workplace from where instructions emanate, or from where the work is organised.

Records are linked by means of a unique personal identification number and are kept at Statistics Denmark. Researchers are authorized to use data with encrypted personal identification numbers, and it is secured so that no analyses identifying any person or enterprise can be transferred outside Statistics Denmark.

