### Study population

Inclusion criteria for the study population are:

• main employment in the construction industry (NACE code = '45');

• employment status as employee or self-employed, that is with the highest income as such during the year;

• job function as manual worker (DISCO-88 code = 7, 8 or 9);

• age from 20 to 59 years - the former time limit due to available OHR-data from the age of 20; the latter time limit due to the possibility of job release scheme from the age of 60;

• male worker - the women will be left out of the study since they constitute less than four percent of the blue-collar workers of the construction industry.

A person enters the population as soon as all of the above criteria are fulfilled, and departs whenever they are no longer met.

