**Plumbers and pipe fitters vs. other manual construction workers**		

**Electricians vs. other manual construction workers**		

**Painters and wall-paper workers vs. other manual construction workers**		

**Unskilled construction workers vs. other manual construction workers**		

## Discussion

Since this is not a randomized study, we cannot rule out that selection into the enterprises may influence the estimates in the sense that cautious people, for example, might prefer employment in large enterprises where safety more often seems to be a priority and different regulatory requirements for safety leads to fewer risk situations. Whereas more reckless people who care less about the potential dangers, or may thrive better with their own risk perception as they themselves decide when to take precautions relative to safety, might prefer employment in small enterprises where fewer legal requirements for safe work must be respected. The effect of enterprise size would then be intensified by the effect of personality type and would bias the estimates away from unity. Conversely, a selection bias towards unity would be the case if, for example, an owner of a micro enterprise focuses on avoiding human and economic losses caused by work-related injuries and therefore is carefully seeking to recruit diligent workers. Moreover, workers in a micro enterprise are probably in closer contact to the management (or owner) compared with those working in a large enterprise and such a close proximity would make it easier for the management to detect risky behaviour in the workplace and dismiss it before injuries occur. We believe, however, that our study group is far more homogeneous than those in most other occupational risk studies and this may counteract potential selection bias. All of the included workers are manual workers belonging to the same industry and most of them are belonging to the same occupational class (skilled workers). The exception is the occupational group 'unskilled construction workers', but this will be controlled for in the analysis.

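### Occupation is adjusted with six named trades and one mixed reference category, so control for occupation among manual workers is incomplete and the Discussion overstates it

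*Protocol article*

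**What the plan says.** - **Aim.** The Background makes occupational control part of the primary aim: size and injury rates are to be related "while controlling for the occupational distribution within the enterprises". It faults earlier studies for lacking that control. It adds that "injury rates differ between occupational categories among blue collar construction workers".
- **Population.** The Study population section requires "job function as manual worker (DISCO-88 code = 7, 8 or 9". Data sources and classifications gives the three major groups; group 8 is "Plant and machinery operators and assemblers".
- **Adjustment.** Statistical analyses controls for age, calendar year and occupation. Its occupation list begins "Occupation unit groups are: Bricklayers and stonemasons (DISCO-88 = 7122); Carpenters and joiners (DISCO-88 = 7124", continues with 7136, 7137 and 7141, and ends with "Unskilled manual workers in construction workers (DISCO-88 = 9313".
- **Reference.** The occupation rows of Table 1 set each of the six against one category, the other manual construction workers.
- **Defence.** The Discussion argues that the study group is homogeneous, most members being skilled. It names unskilled construction workers as the exception, "but this will be controlled for in the analysis".

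**The concern.** The occupation variable has seven levels: six named trades and everyone else. The last level is not an occupation. It joins crafts, machine operators and elementary workers, and the model gives them one common rate. If these subgroups have different injury rates, and their proportions differ between micro, small, medium-sized and large enterprises, part of that difference is attributed to enterprise size. The size ratios are the primary result, and control for occupation is the study's stated advance over earlier work.

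The size ratios under the first null hypothesis are the most exposed. For the second, which compares relative rates before and after July 2002, a difference in mix that stayed constant over time would largely cancel; only a changing mix would matter.

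The same category is also the denominator of all six occupation ratios in Table 1, so those ratios are relative to an undefined mixture.

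**Working it through.** **Step 1: codes side by side (from the document).**

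| DISCO-88 major group | In the population | Has its own term | Falls in the reference |
|---|---|---|---|
| 7 | all | 7122, 7124, 7136, 7137, 7141 | every other craft code |
| 8 | all | none | all of group 8 |
| 9 | all | 9313 | every other group 9 code |

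Five named codes lie in group 7, none in group 8 and one in group 9. No other section subdivides the reference. By the document's own group labels, group 8 and the rest of group 9 are not craft workers, yet neither has a term. The Discussion's single exception therefore does not cover them.

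**Step 2: what this could do to a size ratio (illustration).** The article gives no figure to reproduce: no person-years, injury counts, trade shares or trade-specific rates. All inputs here are assumptions:

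- *s*, the reference category's share of person-years, the same in both size classes: 0.1 to 0.4.
- *R*, the rate ratio between a higher-risk and a lower-risk subgroup inside it: 1.1 to 2. The top value borrows the blue- versus white-collar contrast in the Background, the largest occupational contrast the article quantifies.
- *p*₁ and *p*₀, the higher-risk subgroup's share of the reference category in micro and in large enterprises.
- A true micro-versus-large rate ratio of 1.00, and lower-risk workers with the same rate as the named trades.

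With equal person-time patterns, the main-effects Poisson estimate with the reference left whole is

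(1 + *s·p*₁(*R* − 1)) / (1 + *s·p*₀(*R* − 1)).

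| *R* | *p*₁ / *p*₀ | *s* | Calculation | Estimated ratio (truth 1.00) |
|---|---|---|---|---|
| 1.1 | 20% / 60% | 0.2 | 1.004/1.012 | 0.992 |
| 1.5 | 20% / 40% | 0.1 | 1.01/1.02 | 0.990 |
| 1.5 | 20% / 40% | 0.2 | 1.02/1.04 | 0.981 |
| 1.5 | 20% / 40% | 0.4 | 1.04/1.08 | 0.963 |
| 2 | 20% / 40% | 0.2 | 1.04/1.08 | 0.963 |
| 2 | 10% / 50% | 0.1 | 1.01/1.05 | 0.962 |
| 2 | 10% / 50% | 0.2 | 1.02/1.10 | 0.927 |
| 2 | 10% / 50% | 0.4 | 1.04/1.20 | 0.867 |
| 2 | 30% / 30% | 0.3 | 1.09/1.09 | 1.000 |

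Fitting the Poisson model to expected counts gave the same values for the rows with *R* of 1.5 or 2. At the mildest corner (*R* = 1.1, 20%/40%, *s* = 0.1) the result is 1.002/1.004 = 0.998.

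**Step 3: direction.** If the higher-risk subgroup is commoner in micro enterprises, each ratio inverts: 1.08/1.04 = 1.038 in a moderate case and 1.20/1.04 = 1.154 in the extreme one.

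**Step 4: after the split.** With the two subgroups given separate terms, the fitted size ratio was 1.000 in every scenario fitted. This follows from the set-up, in which the split separates exactly the groups that differ. A split by major group removes confounding between major groups only.

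**The case against.** The best defence is that the main occupational confounder has already been dealt with. The Background's chief complaint about earlier studies is that larger enterprises may employ more white-collar staff; restriction to groups 7-9 removes that, and six occupations are then adjusted for. This stands. What remains is confounding inside one category of manual workers, and it cannot be dismissed because the Background itself says that rates differ among blue-collar occupations.

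It is also fair that the Discussion says only that most workers are skilled, and that homogeneity may counteract selection bias. The sentence needs correcting; it does not invalidate the analysis. The occupation ratios are secondary, and the three trades of special interest (bricklayers, carpenters, plumbers) each have their own term.

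A reader might go further in three ways that the documents do not support:

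- *That the size ratios will be biased, and in a known direction.* It is tempting to suppose that machine operators work mainly in large enterprises, but no section gives the distribution of any occupation by size.
- *That the shift would be large beside the standard error.* No person-years, counts or standard errors are given, so this comparison cannot be made.
- *That complete four-digit codes exist for every worker.* The register is coded in DISCO-88 and the plan uses four-digit codes, but completeness is not stated.

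**Conclusion.** The point holds as one of incomplete control, not of demonstrated bias. The category structure and its mismatch with the Discussion follow directly from the text. The effect on the size ratios is unknown. Under the stated assumptions it is about 1-4% in moderate scenarios and smaller at the mildest corner. In the most extreme scenario it is about 13% downwards, or about 15% upwards when the mix is reversed. It is zero if the make-up of the reference category is the same in all size classes. Because the plan claims this control as part of its primary aim and the remedy is cheap, the change should be made.

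**What to change.** 1. In the models for both hypotheses, replace the single reference with at least three categories: other group 7, group 8, and group 9 other than 9313. Where four-digit coding is available, adjust at minor- or unit-group level instead, pooling rare codes within their own major group.
2. Keep the six trades as rows in Table 1 and state the reference they are compared with, for example other craft workers (group 7).
3. Reword the Discussion so that it says group 8 and the rest of group 9 are also included, and how they are adjusted for.

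The three-way split takes the occupation variable from seven levels to nine, that is, two more parameters from a variable already in the linked data. In a whole-population register the loss of precision should be small. The finer option depends on how complete the four-digit codes are, which should be checked first.
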